All anti-seizure medications aim to achieve therapeutic function by stabilising neuronal networks. Older medications, for example phenobarbitone, had significant adverse effect profiles and could impair cognitive function. Modern anti-seizure medications are much better tolerated and most do not tend to adversely affect cognition, even in older patients [reviewed in 2]. The potent, established anti-seizure medication levetiracetam binds synaptic vesicle protein 2A (SV2A) and inhibits N-type calcium channels to impede synaptic transmission. Intriguingly, SV2A can contribute causally to late-onset AD by mediating the impact of apolipoprotein E4 on amyloid precursor protein (APP) [10].

Initial trials of levetiracetam in epilepsy recruited more than 1000 patients with significant reduction in seizures compared to placebo (Table 1). The drug was well-tolerated with main adverse events being somnolence and fatigue. Subgroup analyses showed that levetiracetam may be particularly efficacious in those aged over 65 years [14]. Levetiracetam has no adverse impact on cognition (including in older subjects) [17]. In individuals with AD and seizures, levetiracetam associated with improvements in attention and verbal fluency as well as better seizure control [18]. It is, however, difficult to determine whether levetiracetam offered additional cognitive benefits beyond that associated with seizure control alone. Also, levetiracetam has no known pharmacokinetic interactions and clinical use over more than a decade has confirmed it to be effective and well-tolerated. Levetiracetam, which is now available as a generic medication, is widely prescribed and there is considerable familiarity with the medication from primary through to tertiary care.

**Table 1 Tab1:** Summary of most relevant clinical trials using levetiracetam (LEV) demonstrating both efficacies and tolerability in epilepsy

Authors and year	Total no. of patients/ no. given LEV	Dose (mg/day)	Impact of LEV on seizure frequency	Significant adverse events
**Ben-Menachem and Falter, 2000** [11]	286/181	3000	Significant benefit of LEV vs. placebo both as add-on (p < 0.001) and as subsequent monotherapy (p = 0.037)	Incidence of adverse events similar in placebo and treatment groups
**Betts et al., 2000** [12]	119/80	2000 or 4000	Significant benefit of LEV vs. placebo at 2000 mg per day (p < 0.05)	Somnolence, asthenia

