**Cereghino et al., 2000** [13]	294/199	1000 or 3000	Significant benefit of LEV vs. placebo (50% responder rate p < 0.001)	Somnolence, asthenia, infection e.g. rhinitis
**Ferrendelli et al., 2003** [14]	78 /78 (patients older than 65 years)	1000 to 3000	Subset analysis of patients who participated in the open label KEEPER trial of a total of 1030 patients.50% responder rate of 76.9%	Somnolence, asthenia Medication well-tolerated in older patients
**Shorvon et al., 2000** [15]	324/212	1000 or 2000	Significant benefit of LEV vs. placebo	No difference in adverse effects vs. placebo. Main side effects: somnolence, asthenia
**Cochrane review (meta-analysis 11 trials incl. above), 2012** [16]	1861 (1565 adults)	1000–4000	Significant benefit to seizures from LEV at every dose compared to placebo Improved cognitive outcomes in adults	Somnolence (RR 1.51; 99% CI 1.06 to 2.17) Infection (RR 1.76; 99% CI 1.03 to 3.02)

Owing to its lack of drug-drug interactions and favourable cognitive profile, levetiracetam is a preferred medication in older people with epilepsy [14]. However, the interest in utilising levetiracetam in AD is founded on animal experiments. Levetiracetam decreases amyloid plaques and alleviates behavioural deficits in an APP-transgenic model of AD [19]. Levetiracetam has also been shown to reduce abnormal electrographic activity and reverse learning and memory deficits in the human APP-transgenic mouse [20]. Such effects were not observed with other anti-seizure medications that were tested [20].

Clinical evaluations of levetiracetam in AD have been limited to people with overt clinical seizures. Levetiracetam is effective at controlling seizures and is well-tolerated in people with epilepsy and AD [18, 21, 22]. Importantly, levetiracetam can improve memory function in people with mild cognitive impairment at risk of developing AD potentially through changes in hippocampal activation [23].

We therefore propose performing a double-blind proof of concept crossover study to evaluate whether levetiracetam may be beneficial to cognition in patients with mild to moderate AD who do not have epilepsy or a history of seizures. To shorten trial duration, refined measures of cognition will be employed to detect any subtle differences in patients while taking levetiracetam compared to placebo.

We hypothesise that:

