### Adverse event reporting and harms {22}

Levetiracetam, as outlined, is a well-tolerated and widely prescribed anti-seizure medication and is a drug of choice in older people with epilepsy. The safety and tolerability profile of levetiracetam is therefore very well-established and familiar to both investigators and General Practitioners. Common side effects from levetiracetam include asthenia, an effect on sleep and an effect on mood. Gastrointestinal disturbance, change in weight and rash are occasionally reported. The effect of levetiracetam on mood in patients with AD is captured within the data that will be collected from recruited participants. The full list of potential expected adverse events is listed in the Summary of Product Characteristics [33].

Given the familiarity with levetiracetam in both tertiary and primary care and, in particular, given that levetiracetam is being used at its licenced dose, non-serious adverse events will not be recorded within the ILiAD study unless they lead to withdrawal from treatment. Solicited and unsolicited adverse events are listed in Table 3 below:

**Table 3 Tab3:** Solicited and unsolicited potential adverse events associated with levetiracetam

Adverse event	Solicited	Unsolicited
**Asthenia**		x
**Change in weight**		x
**Cough**		x
**Effect on mood/behaviour**	x	
**Effect on sleep**		x
**Gastrointestinal disturbance**		x
**Nasopharyngitis**		x
**Rash**	x	

SAEs will be recorded from the time of taking informed consent to 28 days following the last administration of study medication. The participants in this study are from an older population and may have co-morbidities beyond Alzheimer’s disease. An event that is part of the natural course of the disease (i.e. disease progression or admission for standard treatment) will not be reported as an SAE. However, if the progression of the underlying disease is greater than that which would normally be expected, or if the investigator considers that there may be a causal relationship between the IMP or protocol design/procedures and the disease progression, then it must be reported.

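### Table 3 leaves asthenia and sleep effects unsolicited, although the protocol's own evidence puts somnolence and asthenia/fatigue first among the drug's adverse effects

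*Protocol article*

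**What the plan says.** The section Adverse event reporting and harms {22} announces that "Solicited and unsolicited adverse events are listed in Table 3 below". Table 3 has eight rows. Two carry their mark in the Solicited column: rash and mood ("Effect on mood/behaviour x"). The other six carry it in the Unsolicited column: asthenia, change in weight, cough, sleep ("Effect on sleep x"), gastrointestinal disturbance and nasopharyngitis. Somnolence is not named; effect on sleep is the nearest row.

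The same section says "Common side effects from levetiracetam include asthenia, an effect on sleep and an effect on mood", and then "Gastrointestinal disturbance, change in weight and rash are occasionally reported".

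Background and rationale {6a} summarises the epilepsy trials thus: "The drug was well-tolerated with main adverse events being somnolence and fatigue". One trial row of Table 1 reads "Main side effects: somnolence, asthenia". The meta-analysis row gives "Somnolence (RR 1.51; 99% CI 1.06 to 2.17".

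Four other statements bear on the point:
- Outcomes {12} makes side effects against placebo a secondary outcome, describes finding them as clinically essential, and has them raised at every study contact.
- Subsequent visits brings patients and carers to the site at weeks 8 and 20, with detailed side-effect reporting. It also sets safety checks at weeks 2, 4, 14 and 16.
- The harms section says that a non-serious adverse event is recorded only if it leads to withdrawal from treatment.
- The main-text Discussion says that all adverse events will be recorded.

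**The concern.** The list of solicited events does not follow the evidence that the protocol cites. The best-documented effects of the drug fall in the unsolicited column, while rash, described as only occasional, is solicited. Events that nobody asks about by name tend to be reported less completely, and participants here have impaired memory.

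Two uses of the data are exposed. Side effects against placebo are the first secondary objective and the first secondary outcome. Tolerability is also a stated hypothesis, and the Abstract allows good tolerability, with or without stabilised memory, to justify moving to a larger study. If the expected effects are incompletely ascertained, that criterion becomes easier to meet.

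**Working it through.** The point rests on comparing passages. No figure in the protocol is disputed.

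**Step 1. Evidence against classification.**

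| Effect | Background and Table 1 | Harms section, text | Table 3 |
|---|---|---|---|
| Asthenia/fatigue | Fatigue a main event; asthenia in 4 of 5 individual trial rows | Common | Unsolicited |
| Somnolence/sleep | Somnolence a main event; in 4 of 5 individual trial rows; RR 1.51 in the meta-analysis | Sleep effect common | Sleep unsolicited; somnolence not named |
| Mood/behaviour | Not in Table 1; named in the hypotheses | Common | Solicited |
| Rash | Not in Table 1 | Occasional | Solicited |
| Gastrointestinal, weight | Not in Table 1 | Occasional | Unsolicited |

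The four trial rows include the subset of patients older than 65. Of the two main event types in the Background, 0 of 2 are solicited by name. Of the three effects the harms section calls common, 1 of 3 is solicited. Of the three it calls occasional, 1 of 3 is solicited. The column an item falls in therefore does not track how often the protocol expects it.

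**Step 2. Does the enquiry at each contact cure this?** Only in part. Outcomes {12} provides an active enquiry, and carers are present at key visits. But Table 3 separates solicited from unsolicited items within a study that already has that enquiry. If the general question made every item solicited, the table would mean nothing. Read consistently, asthenia and sleep effects are captured only if the participant or carer raises them in answer to a general question.

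**Step 3. Would moving the rows be enough?** No. Under the harms section's recording rule, a non-serious report of sleepiness that does not end treatment is not recorded, solicited or not. Outcomes {12} needs such reports for its comparison with placebo, and the Discussion says that they are kept. The three statements cannot all hold.

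**Step 4. Can the under-count be sized?** Not from the documents, which give neither a placebo rate of somnolence (p0) nor the share of events captured without specific questions (c). For illustration only, with 30 participants observed on each treatment and the cited RR of 1.51:

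recorded excess = 30 × p0 × (1.51 − 1) × c

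| Assumed p0 | c = 100% | c = 50% | c = 25% |
|---|---|---|---|
| 5% | 0.77 | 0.38 | 0.19 |
| 10% | 1.53 | 0.77 | 0.38 |
| 20% | 3.06 | 1.53 | 0.77 |

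The RR is itself uncertain. At p0 = 10% and full capture, its 99% limits give 30 × 0.10 × 0.06 = 0.18 to 30 × 0.10 × 1.17 = 3.51 participants. If c is the same on both treatments it cancels from the ratio, which stays at 1.51; only the counts and the absolute difference shrink.

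**The case against.** The strongest reply is that the protocol already looks for side effects actively. They are raised at every contact, there are early safety checks in each period, adverse effects are recorded at weeks 12 and 24, and a reliable carer is an entry requirement. The exact wording of the enquiry would sit in the case report form or the full protocol, which are not shown. This stands to the extent that a reader who inferred that the endpoint simply waits for people with Alzheimer's disease to volunteer symptoms would be going beyond the text. It does not remove the point, because Table 3 is an explicit item-by-item choice and not a detail left to another document.

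A second reply is that numbers are small whatever is asked: even with full capture, the illustration gives an excess of about 1 to 3 participants, which 30 people cannot resolve. The RR also comes from doses of 1000 to 4000 mg/day, and this trial's 1000 mg/day is at the bottom of that range. Two Table 1 trials report adverse events similar to placebo. All of this is fair and limits what can be said about size. Complete description of tolerability is still the purpose of a pilot's safety outcome.

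A third reply is that soliciting mood is well founded, since mood is a hypothesis, an objective and an outcome. That is accepted; nothing here argues for dropping it.

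A further reading is tempting: that sedation could hide a cognitive benefit at weeks 8 and 20, and that asking about it would reveal this. The documents do not support it. The Background says that the drug does not harm cognition, including in older people. The primary comparison estimates the net effect, and a yes/no answer given after randomisation could not separate a masked benefit from no benefit.

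**Conclusion.** The mismatch is real and is stated in the protocol itself. Table 3 does not solicit the effects that the Background names as main, and it solicits one of the three that the harms section calls common. The consequence is a risk of under-ascertainment in a secondary outcome and in the tolerability criterion for a larger study; the primary analysis is not invalidated. The under-count has no derivable size, and the figures above depend on assumed placebo and capture rates. A reader might also infer a bias in the relative risk. That would require capture to differ between treatments, which the documents do not show and blinding makes less likely. The conclusion assumes that solicited in Table 3 means asked about by name. If it does not, the table needs correcting for that reason instead. This should be changed, and it is inexpensive to change.

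**What to change.** 1. In Table 3, mark asthenia/fatigue and effect on sleep as solicited, and name somnolence in the sleep row or give it its own row.
2. Put the same scripted yes/no questions on these items to participant and carer at each scheduled contact in both periods, including weeks 8 and 20, and record the answers.
3. Reconcile the harms section's rule on non-serious events with Outcomes {12}, which compares side effects with placebo, and with the Discussion, which says that all adverse events are recorded. Without this, the first two changes have no effect on the data.
4. Treat the sedation answers at the efficacy visits as descriptive context for the touchscreen score only.

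The cost is two or three extra questions at contacts that already raise side effects, and more minor reports to process in both periods. No extra visit is needed.

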#### Secondary

Determination of side effects from levetiracetam in the study population compared to placebo. Anti-seizure medications are generally well-tolerated in people with epilepsy, but are not routinely administered to people who have not had a seizure. It is therefore clinically essential to determine if there are side effects in this patient group. This will be enquired about at each study contact.Determination of the effect on mood of levetiracetam in the study population compared to placebo using standardised scales such as Neuropsychiatry Index. Given that levetiracetam can have an adverse effect on mood, this will be specifically evaluated and monitored throughout. Principal comparisons will be between the start and end of each arm of the study.Determination of the effect on quality of life from levetiracetam in the study population compared to placebo using standardised scales such as the BADLS, EQ-5D and DSRS index (compare end of arm 1 to baseline and end of arm 2 to end of arm 1). Even were levetiracetam to not show an advantage on cognitive measures, were it to improve quality of life in people with AD that may make it a worthwhile treatment.Assessment and modelling of the EEG prior to starting levetiracetam and correlation with response to levetiracetam. It may well be that levetiracetam is not suitable for all people with AD. EEG could offer a simple non-invasive biomarker to better determine who may benefit from levetiracetam and similarly who may experience side effects. The EEG is performed at baseline and will be modelled and correlated with outcomes for each participant at study end.

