## Oversight and monitoring

### Composition of the coordinating centre and trial steering committee {5d}

The lead site is the John Radcliffe Hospital, Oxford University Hospitals NHS Foundation Trust. An annual report will be submitted to the Monitor who will also have access to all study data on request. The Oxford University Hospitals Trust / University of Oxford Trials Safety Group (TSG) will conduct a review of all SAEs for the trial reported during the quarter and cumulatively. The aims of this committee include:
To detect any trends, such as increases in un/expected events, and take appropriate actionTo seek additional advice or information from investigators where requiredTo evaluate the risk of the trial continuing and take appropriate action where necessary

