Reportable SAEs will be reported on the SAE reporting form to the trial monitor within 24 h of the Site Study Team becoming aware of the event. The trial monitor will perform an initial check of the report, request any additional information, and ensure it is reviewed by the Medical Monitor on a weekly basis. It will also be reviewed at the next Trial Safety Group meeting. All SAE information must be recorded on an SAE form and emailed to CTRG. Additional and further requested information (follow-up or corrections to the original case) will be detailed on a new SAE Report Form and faxed/emailed to CTRG.

All SUSARs will be reported by the CI to the relevant Competent Authority and to the REC and other parties as applicable. For fatal and life-threatening SUSARS, this will be done no later than 7 calendar days after the Sponsor or delegate is first aware of the reaction. Any additional relevant information will be reported within 8 calendar days of the initial report. All other SUSARs will be reported within 15 calendar days. Treatment codes will be unblinded for specific participants.

Principal investigators will be informed of all SUSARs for the relevant IMP for all studies with the same Sponsor, whether or not the event occurred in the current trial.

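### Serious events judged to be natural course of Alzheimer's disease leave SAE reporting, so a misattributed drug effect would miss safety review; record them all and limit the exemption to expedited reporting

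*Protocol article*

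**What the plan says.** The rule is in the protocol article under Adverse event reporting and harms {22}. SAEs are recorded from consent until 28 days after the last dose. Anything counted as "part of the natural course of the disease (i.e. disease progression or admission for standard treatment) will not be reported as an SAE". Two conditions restore the duty to report: "if the progression of the underlying disease is greater than that which would normally be expected", or where "the investigator considers that there may be a causal relationship between the IMP or protocol design/procedures and the disease progression".

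The same section then sets the route: "Reportable SAEs will be reported on the SAE reporting form to the trial monitor within 24 h". The trial monitor checks the report and must "ensure it is reviewed by the Medical Monitor on a weekly basis", and it also goes to the next TSG meeting. A further sentence reads "All SAE information must be recorded on an SAE form and emailed to CTRG".

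Under Composition of the coordinating centre and trial steering committee {5d}, the TSG "will conduct a review of all SAEs for the trial reported during the quarter and cumulatively". Section {21a} says that no data monitoring committee was thought necessary.

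The secondary outcomes under Outcomes {12} include "Determination of side effects from levetiracetam in the study population compared to placebo", with enquiry at every contact.

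**The concern.** The exemption is a filter by presumed cause, applied by a blinded investigator before an event reaches anyone who looks across participants. Section {22} lists asthenia, sleep effects and mood effects as common with levetiracetam, and each can resemble a symptom of dementia. If such an effect became serious and was read as ordinary Alzheimer's disease, it would not be a reportable SAE.

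Two things are at stake. The first is review: the Medical Monitor and the TSG look for problems among reported SAEs, and no data monitoring committee stands behind them. The second is the comparison with placebo. In a blinded crossover, events truly due to the disease are expected in both periods, so the comparison does not need them removed. Removing events by attribution can, however, take out some that the drug caused, and those arise from levetiracetam exposure. The effect would be to make levetiracetam look safer than it is. The Abstract names good tolerability as one of the findings that could lead to a larger study.

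**Working it through.** No figure in the plan is at issue, so the check is mainly a reading of the sections against each other, followed by exposure arithmetic that sizes the remedy.

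**1. What is exempt.** The condition is that the event is part of the natural course of the disease. Progression and admission for standard treatment are the kinds named within that condition. An event that the investigator suspects is drug-related does not meet it.

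**2. What the exemption removes.** The 24-hour route starts from reportable SAEs, and the TSG reviews SAEs that were reported. An exempted event enters neither.

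**3. Whether an exempted event is still recorded.** The text points both ways.

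| Place | Reading |
|---|---|
| {22}, SAE window | SAEs are recorded from consent to 28 days after the last dose |
| {22}, exemption | Exempted events are not reported as SAEs; recording is not mentioned |
| {22}, SAE form | All SAE information goes on a form; whether that covers exempted events is not said |
| {22}, non-serious events | Not recorded unless they lead to withdrawal from treatment |
| Discussion | All adverse events will be recorded; this conflicts with {22} on non-serious events but not on serious ones |

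The article does not settle whether exempted serious events are kept, or on what form.

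**4. What must go wrong for an event to be lost.** All of the following are needed: the event is serious; levetiracetam contributed to it; the investigator does not suspect this; and, if it looks like progression, it is judged no worse than expected. Trial design {8} does not anticipate marked progression during the study, so progression bad enough to be serious would usually exceed expectation and have to be reported.

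**5. What else would show it.** The Neuropsychiatric Inventory (NPI) and the Bristol Activities of Daily Living Scale (BADLS) are measured at baseline, and all baseline efficacy measures are repeated at weeks 8 and 20. Neither scale passes through a causal judgement. Side effects are asked about at each contact.

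**6. Scale of the remedy.** Inputs: Table 2 has tablets in weeks 1 to 11 of each 12-week period and none in week 12; the crossover is at week 12; recording runs to 28 days (4 weeks) after the last dose; 30 participants are planned, with a minimum of 24 completers.

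- Last tablet: 12 + 11 = end of week 23.
- End of SAE window: 23 + 4 = week 27 from randomisation. The consent-to-randomisation interval is not stated and is left out.
- SAE window, 30 participants: 30 × 27 = 810 participant-weeks; 810 / 52.18 = 15.5 participant-years.
- SAE window, 24 participants: 24 × 27 = 648; 648 / 52.18 = 12.4 participant-years.
- Time on levetiracetam tablets: 30 × 11 = 330 weeks, or 330 / 52.18 = 6.3 participant-years; with 24, 264 / 52.18 = 5.1.

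These figures bound the paperwork. They do not measure lost events, for which the documents give no rate, and none is assumed here.

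**The case against.** The strongest reply is that a natural-course exemption with a must-report override is a deliberate choice and contradicts nothing. Several safeguards stand around it. Greater-than-expected progression is reportable without any causal judgement. The causal condition needs only a possible link. Withdrawals and serious side effects are handled as if the participant were on active drug ({11b} and {17b}). Exclusion criteria {10} remove major depression, significant behavioural disturbance and other severe illness. The placebo comparison is not said to rest on SAE forms alone. The form used for an exempted event is also the kind of detail that a condensed article leaves to the full protocol.

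Most of this stands, and it is why the risk is small. It does not remove the filter. The assume-active rules govern how withdrawals and recognised side effects are handled, not whether an event is classed as disease. Section {11b} lists disease progression separately from adverse events as a reason to discontinue, and promises follow-up to resolution only for adverse-event withdrawals.

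Two stronger readings are tempting and are not supported. A reader might infer that the override is defective because both its conditions name progression and neither names admissions, so that a drug-related admission could go unreported even when suspected. It could not: a suspected drug-related admission is not natural course and was never exempt. Adding admissions to the causal condition would not catch misattribution either. A reader might also infer that exempted serious events are not recorded at all. The article withholds them from reporting; on recording it is unclear.

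**Conclusion.** The point holds in a limited form. A levetiracetam-related serious event misattributed to Alzheimer's disease would miss Medical Monitor and TSG review, and might not be counted in the side-effect comparison with placebo. The first part follows from the stated reporting route. The second is only possible, because it depends on whether exempted events are recorded and on what the comparison draws from.

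The size is unknown and probably small. That judgement assumes that investigators apply the greater-than-expected condition as written, and that progression stays as slow as the article anticipates. The primary outcome and the sample size are not affected. This is a worthwhile cheap improvement, and the documents do not show that any event has been or will be lost.

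**What to change.** In section {22}, state that every event meeting a seriousness criterion is recorded on the SAE form whatever its presumed cause, tabulated by treatment period, and included in the TSG's cumulative review. Limit the natural-course exemption to expedited (24 h) reporting. Naming admissions in the override is optional clarification only.

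The cost is a wording change and a few extra forms, confined to exempted serious events over about 15.5 participant-years after randomisation. The downside is paperwork for events that really are due to the disease.
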